**Methods:**

This study will use a nonrandomized controlled trial design with a qualitative evaluation to assess feasibility and acceptability. Data will be collected through student surveys, student focus groups, and teacher reflection journals. Two schools in New South Wales, Australia, will participate by implementing the TPSR framework in their programs. Schools will include classes in stages 3 and 4 of the intervention, involving approximately 90 students from each school. Both schools are located in Sydney, New South Wales: one is a government high school, and the other is an independent K-12 school. To address feasibility and accessibility concerns, the intervention will be delivered during regularly scheduled PE classes. It will be facilitated by students’ regular PE teachers, who will also participate in ongoing professional development and be involved in a co-design process with the research team. Primary outcomes include reporting on personal responsibility, social responsibility, and leadership behaviors, measured using two tools: (1) the Tool for Assessing Responsibility-Based Education and (2) the Personal and Social Responsibility Questionnaire. A secondary outcome, enjoyment, will be assessed using the Physical Activity Enjoyment Scale–Physical Education version. Feasibility and accessibility will also be examined as secondary outcomes.

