**Results:**

This intervention study will demonstrate the impact of TPSR on social outcomes among Australian school participants. Students will also receive a briefing, and parental permission will be sought before intervention commencement. Students will be involved in the intervention for the duration of term 3 (10 weeks).

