### Study Design

The protocol was developed according to the SPIRIT (Standard Protocol Items: Recommended for Interventional Trials) statement (Multimedia Appendix 1).

The study will use a nonrandomized controlled trial design with a qualitative evaluation to assess feasibility and acceptability. This method has been chosen for several reasons. First, one of the criticisms against the TPSR model is that it favors qualitative studies and has been underresearched using quantitative methodologies [11]. To address this, we will use both qualitative and quantitative methods in this study. The concern regarding the limited use of quantitative approaches was echoed in a systematic review on TPSR interventions that found that only 4 of the 22 included studies used exclusively quantitative methods, questioning the validity of the framework outside of qualitative research [26]. Studies have consistently called for greater use of quantitative analysis of the TPSR framework in research [10,11,26]. Furthermore, to obtain the most accurate representation of the effect of the framework in Australian schools, teachers, and students, this approach is deemed most suitable because it uses both qualitative and quantitative analysis and is able to factor in a complex landscape such as education [27]. In this study, data will be collected through student surveys, focus groups, teacher reflection journals, and the Tool for Assessing Responsibility-Based Education (TARE).

We will recruit at least 6 classes from each school participating in the intervention, which will amount to approximately 3 classes in the control group and 3 in the experimental group (Figure 1).

Upon recruitment of the schools and selection of individual classes by each principal, researchers will collaborate with intervention facilitators to implement the TPSR framework during the intervention “season.” Table 1 presents example strategies that can be implemented in a TPSR study and will be shared with teachers during the co-design process.

A timeline of the intervention is presented in Table 2.

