### Participants

The participants in this study will be students from years 5, 6, and 8. Each intervention group in the study will need to have 77 students and a matched control group of the same size to detect 2-tailed statistical significance (*P*<.05) with 80% power (1−β=0.8). Two schools in the western suburbs of Sydney have been recruited to participate in the study: one is a government high school, and the other is an independent K-12 school. They have been chosen through professional networks who expressed interest in the TPSR study. Students in NSW generally participate in 1 PE lesson per week, which is where the intervention will take place. PE lessons in NSW high schools are delivered to students from years 7 to 10 and focus on skills development, alongside one or two sport lessons focused on game play.

Consent will be obtained from parents, students, and the school principals in line with the ethics requirements of the University of Sydney. Participants’ personal information and school names will be deidentified in all publications arising from the study. Students and teachers will also be briefed on the intervention before study commencement and given the opportunity to ask questions. Participants will be allowed to withdraw from the intervention at any time. All data collected, including data from focus interviews, surveys, meeting minutes, and consent forms, will be stored securely and encrypted with a password. If parents request details of intervention results, a lay summary will be provided.

Fidelity and acceptability will be addressed through teacher expertise and training, intervention location, timetabling, and time spent on the intervention. Teachers will participate in a professional development program before starting the intervention. The purpose of this program is to familiarize teachers with the TPSR framework and to facilitate the co-design of strategies and activities to integrate the framework into programs. This approach also means that students do not have to build relationships with or adapt to outside facilitators. Furthermore, it does not incur additional funding for the school or research team. The professional development program will comprise a 3-hour, face-to-face learning block before the intervention and ongoing check-ins with teachers using Zoom (Zoom Video Communications, Inc) for the duration of the intervention.

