The intention of the co-design process is to limit disruption to teachers and their practice as well as to create a mutually agreed-upon implementation of the TPSR framework in existing units. The co-design process allows both parties to benefit from sharing information that aims to improve currently established protocols and promotes sustainable practice within the school and with teachers [28]. Co-design principles can be applied at any stage of an intervention but may target three main components: (1) defining the problem, (2) designing a solution, and (3) implementation [29]. Throughout this intervention, teachers will work with researchers to identify social issues at their school; they will then work with researchers to apply TPSR principles to address these issues; and, finally, they will be involved in facilitating PE lessons that implement these principles with students. The co-design process aims to “share power” between the 2 parties taking part in the research with the mutual aim of improving outcomes [29]. This process will enable the research team and teachers to navigate the intervention in a collaborative manner, strengthening the planning process before intervention commencement.

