#### Quantitative Analysis

Quantitative data from the PSRQ, PACES-PE, and TPSR will be analyzed using SPSS software (version 30.0; IBM Corp). Internal consistency of the scales will be assessed using Cronbach α. The PSRQ will assess students’ self-perceived levels of personal and social responsibility, and the PACES-PE will assess enjoyment in PE. ANOVA will be conducted to compare mean scores before and after the intervention for both questionnaires. TARE data will be collected through lesson observations by the research team 3 times during the 10-week intervention period, and interrater reliability will be assessed using Cohen κ. Frequencies and mean scores of the TPSR strategies will be examined descriptively and across time to explore implementation fidelity. A repeated measures multivariate ANOVA will be performed to provide a more complex analysis of the findings and a more comprehensive view of how the intervention affects multiple variables simultaneously.

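### No school term or by-school contrast is named for a trial nested in two volunteer schools, while the aim is worded for Australian schools

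*Protocol article*

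**What the plan says.** Participants describes one government high school and one independent K-12 school in western Sydney: "They have been chosen through professional networks who expressed interest in the TPSR study". Study Design plans at least six classes per school, "which will amount to approximately 3 classes in the control group and 3 in the experimental group". TPSR and control classes therefore sit side by side within each school.

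Delivery is adapted locally. In the co-design process "teachers will work with researchers to identify social issues at their school", and the framework is then applied to those issues. Intervention Design adds that lesson length depends on the school.

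For size, Participants states: "Each intervention group in the study will need to have 77 students and a matched control group of the same size". The abstract has the trial "involving approximately 90 students from each school".

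For analysis, Quantitative Analysis states: "ANOVA will be conducted to compare mean scores before and after the intervention for both questionnaires". A repeated measures MANOVA follows. No model factors are listed. School type appears under Outcomes as a baseline characteristic, with no analytic use given.

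On scope, Objectives speaks of impact in the Australian context, and Study Design of the framework's effect in Australian schools, teachers and students. The abstract adds: "This intervention study will demonstrate the impact of TPSR on social outcomes among Australian school participants". The predicted limitations under Strengths and Limitations cover only delivery confined to PE and the resulting doubt about transfer.

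**The concern.** School is a stratum built into the design, and there are only two. They differ in sector, age range, possibly lesson length, and the local adaptation of TPSR. If all classes enter one analysis without school, the result is a single average. An effect confined to one school would then appear as a general one, and the stated aim invites readers to take it as TPSR's effect in Australian schools.

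A second consequence follows from the word approximately in the 3:3 plan. Classes are not randomized; principals select them. If the split is unequal in either school, the two arms contain different mixes of the schools, and any school difference in the analysed score enters the arm contrast. A school term removes that component.

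**Working it through.** **1. The plan's own figure.** Inputs from Participants: 77 per group, 1:1, "to detect 2-tailed statistical significance (*P*<.05) with 80% power". No effect size or SD is given, so 77 cannot be reproduced forward. Back-solving with SD = 1:

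- d = (1.960 + 0.842) × √(2/77) = 2.802 × 0.161 = 0.45 (0.454 with the t distribution).
- Going forward, d = 0.45 gives 78 per group by the normal approximation.

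The figure is consistent with d of about 0.45, but that value is inferred.

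**2. Do the figures point to a joint analysis?** The target is 77 + 77 = 154.

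- Reading A, about 90 per school over both arms: one school falls short (90 < 154) and both together suffice (180 ≥ 154). This gives 45 per arm per school and 90/6 = 15 per class.
- Reading B, 77 per arm within each school: 154 per school, or 77/3 ≈ 26 per class. This conflicts with 90 per school if that figure counts both arms, but not if it counts TPSR students only.

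Reading A suggests a joint analysis. The text settles neither.

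**3. What an overall estimate can hide** (Reading A, equal schools, SD = 1, students treated as independent).

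- Effects of 0.9 and 0: average (0.9 + 0)/2 = 0.45. Power with 90 per arm = Φ(0.45/√(2/90) − 1.960) = Φ(3.019 − 1.960) ≈ 86%.
- Effects of 0.8 and 0: average 0.40, power about 77%.
- One school alone at d = 0.4515: Φ(0.4515/√(2/45) − 1.960) = Φ(0.182) ≈ 57%.

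Class clustering lowers these figures. With 15 per class and an assumed ICC of 0.05, the design effect is 1 + 14 × 0.05 = 1.70, the effective size is 90/1.70 = 52.9 per arm, and overall power at d = 0.4515 is about 64%. The 0.9/0 split is an illustration, not a forecast.

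**4. How precise by-school contrasts would be** (15 per class, ICC 0.05, both assumed for analysis).

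- Variance of a class mean: v = 0.05 + 0.95/15 = 0.113.
- Half-width of the 95% interval in one school, 3 versus 3 classes: t(0.975, 4 df) × √(2v/3) = 2.776 × 0.275 = 0.76 SD.
- Half-width for the difference between the two schools' effects: t(0.975, 8 df) × √(4v/3) = 2.306 × 0.389 = 0.90 SD.
- Even without clustering, power to detect a between-school difference of 0.45 is Φ(0.45/√(4/45) − 1.960) ≈ 33%.

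**5. Unequal class splits.** Let pT and pC be the shares of TPSR and control classes that come from one school, and δ the school difference in the analysed score. Without a school term, δ adds (pT − pC) × δ to the arm contrast.

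- 3:3 in both schools: (3/6 − 3/6) × δ = 0.
- Illustration with 4:2 in one school and 3:3 in the other: (4/7 − 2/5) × δ = 0.171δ. For an assumed δ of 0.3 to 0.5 SD this is 0.05 to 0.09 SD.

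**6. School and age.** Participants places high-school PE in years 7 to 10, and the sample is years 5, 6 and 8. Years 5 and 6 can therefore come only from the K-12 school, so a difference between the schools is partly a difference in age.

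**The case against.** The strongest reply is that a condensed article lists tests, not model factors. Quantitative Analysis names no factor at all, not even trial arm, so its silence on school is not a decision to pool. A full protocol or SAP may hold a by-school analysis. That stands: joint analysis is an inference from the numbers. It does not answer the wording of the aim or the missing limitation, which the article itself fixes. The abstract's phrase about school participants can fairly be read as the students taking part, and the abstract discloses two Sydney schools. The wording in Objectives and Study Design is broader.

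Several stronger readings are tempting and should not be drawn:

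- *The schools receive two different packages.* Table 2 gives one timeline with shared named components, the Table 1 strategies go to all teachers, there is one professional development program, and TARE observation checks fidelity. The text supports local adaptation of one framework.
- *The arm contrast is biased by school.* Controls sit within each school, so school is not confounded with arm if the 3:3 split holds.
- *A by-school difference would show that one school's adaptation works.* It could not be separated from age, school type or lesson length.
- *Omitting school inflates the standard error, or leaves almost no degrees of freedom.* The first needs a class-level analysis that is not stated and a school gap that cancels in change scores if it is stable. The second concerns formal inference to other schools, which the analysis section does not plan.

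It is also fair that by-school estimates will be too imprecise to settle whether the effects differ. That is why they should be labelled descriptive.

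**Conclusion.** The point holds as one of analysis specification and scope of conclusion. An existing design stratum, already recorded, has no stated place in the analysis, and the aim reaches further than two volunteer schools allow. If the classes are analysed together, an effect of 0.8 to 0.9 SD in one school and none in the other would give an overall 0.40 to 0.45 SD, significant with about 77% to 86% power before clustering is allowed for, and nothing in the named output would show the split. This rests on Reading A of the sample figures, equal school sizes and SD = 1. The possible contamination of the arm contrast is zero under an exact 3:3 split and arises only if the split departs from it. If 77 per arm applies within each school, the case for assuming a joint analysis weakens, but the points on scope and the missing limitation remain.

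**What to change.** In Quantitative Analysis, include school as a fixed stratum. Report the TPSR-minus-control difference for School A and School B with confidence intervals, labelled descriptive, next to the overall estimate. State there that school cannot be separated from age, school type or local adaptation.

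In Objectives, Study Design and the abstract, word the conclusion as the average effect in these two volunteer schools. Add to Strengths and Limitations that two schools recruited through professional networks do not support a claim about NSW or Australian schools in general.

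The cost is one model term, one table and some rewording; no new data are needed. The downsides are wide by-school intervals (about ±0.76 SD on the assumptions above), a narrower claim, and the need to code the schools and check the table against the deidentification undertaking.

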### Measurement Tools

The Personal and Social Responsibility Questionnaire (PSRQ) will be used to measure the primary outcomes of the study: personal responsibility, social responsibility, and leadership. This questionnaire has been used in previous TPSR studies and has been deemed valid and reliable [30,31]. It consists of 14 items split into 2 categories (personal responsibility and social responsibility) [30]. Participants will complete the PSRQ in the pretest and posttest phases of the intervention and will be assured that there are no right or wrong responses and that their responses will remain anonymous. The TARE is an observational tool aligned with the TPSR model. The second part focuses on whether teachers have included elements such as modelling respect and setting expectations within their lessons [32]. The secondary outcomes of the study will be enjoyment, feasibility, and acceptability. These outcomes will be measured using the Physical Activity Enjoyment Scale–Physical Education version (PACES-PE), which is an 11-item measurement tool designed to measure enjoyment levels in adolescent children using a Likert scale and revised, student-friendly questions [33]. The PACES-PE has been used in PE-based studies previously and demonstrated positive results in female adolescent populations, particularly through the link between enjoyment and increased rates of physical activity [33].

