### Outcomes

The primary outcomes addressed within the intervention are personal responsibility, social responsibility, and leadership, reflecting the levels of the TPSR framework. The secondary outcomes include enjoyment, feasibility, and acceptability. To obtain a comprehensive analysis of the TPSR framework within a school system, the proposed outcomes will provide valuable insights into how the framework influences student behavior and overall intervention effectiveness.

Baseline characteristics will include age, gender, boarding status (boarding vs nonboarding), school type, and SES (via postcode).

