### Intervention Design

This intervention will focus on providing opportunities for students to develop social skills in PE classes. Teachers will act as facilitators, and researchers will codevelop and adapt the intervention programs with them using a co-design process. A teacher professional development program will be administered before intervention commencement to ensure that teachers are familiar with the TPSR framework. Students will take part in focus groups before and after the intervention and will complete surveys measuring social outcomes. The researchers will be available for communication with teachers to maintain intervention integrity and to ensure that issues are addressed efficiently. Teachers will run their PE lessons with the TPSR framework embedded within their existing programs, minimizing additional workload. Examples of TPSR strategies that may be featured within lessons are provided in Table 1.

Before intervention commencement, students and teachers from the participating schools will complete preintervention testing, which will include surveys. Students at each school will then take part in the 10-week intervention and complete a postintervention test similar to the preintervention test. Focus groups will also be conducted during the posttest period. There will be a follow-up 5 weeks after the intervention. In line with the mandated requirements of the schools, students will participate in 1 PE lesson per week, which is standard practice in NSW schools. The duration of each lesson will depend on the school, with 45 to 60 minutes being typical in NSW schools. Social outcomes (personal responsibility and social responsibility) will be the primary focus of the intervention, as per the measurement tool.

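### Leadership is one of three primary outcomes, but as the protocol is written it has no defined score and no pre-post or between-group analysis

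*Protocol article*

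**What the plan says.** The Outcomes section states: "The primary outcomes addressed within the intervention are personal responsibility, social responsibility, and leadership, reflecting the levels of the TPSR framework". Measurement Tools gives the instrument for all three; the PSRQ "will be used to measure the primary outcomes of the study: personal responsibility, social responsibility, and leadership". Shortly afterwards it describes that questionnaire: "It consists of 14 items split into 2 categories (personal responsibility and social responsibility". Quantitative Analysis repeats the two-construct description: "The PSRQ will assess students’ self-perceived levels of personal and social responsibility".

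The Methods paragraph of the abstract gives a different account of the instruments. There the three primary outcomes are "measured using two tools: (1) the Tool for Assessing Responsibility-Based Education and (2) the Personal and Social Responsibility Questionnaire". In the body of the article, Measurement Tools calls the TARE observational and describes only its second part, which concerns what teachers include in their lessons. Table 2 places it in weeks 2, 5 and 8 of term 3. Quantitative Analysis says how its data will be used: "Frequencies and mean scores of the TPSR strategies will be examined descriptively and across time to explore implementation fidelity".

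Intervention Design mentions only two constructs: "Social outcomes (personal responsibility and social responsibility) will be the primary focus of the intervention, as per the measurement tool".

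**The concern.** A primary outcome needs an instrument that yields a score, and an analysis that turns the score into an effect. The article gives both for the two responsibility outcomes. For leadership it names an instrument that, on its own description, has no leadership category. The second tool, named only in the abstract, is used elsewhere for a different purpose.

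If the plan is followed as written, the trial will produce no leadership effect although leadership is promised as a primary result. Relying on the TARE strategy scores instead would be circular. They record whether the TPSR strategies were delivered, so delivering the intervention would itself raise the score, whether or not students changed.

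**Working it through.** The question is which outcome is matched to which instrument, score and analysis. It is settled by setting the sections side by side.

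**1. Trace each primary outcome.**

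| Primary outcome | Instrument assigned | Score described | Pre-post comparison stated |
|---|---|---|---|
| Personal responsibility | PSRQ (Measurement Tools); PSRQ and TARE (abstract) | Yes, a PSRQ category | Yes, ANOVA of the questionnaires |
| Social responsibility | Same | Yes, a PSRQ category | Yes, ANOVA of the questionnaires |
| Leadership | Same | None | None |

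Outcomes with both a score and a comparison: 2 of 3. Without either: 3 − 2 = 1, which is leadership.

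**2. Test whether the TARE fills the gap.**
- Timing: all three observations fall within delivery (term 3, weeks 2, 5 and 8). Table 2 lists none in term 2 week 8, when the surveys are given before the intervention, and none in term 3 week 10, when they are repeated. A pre-post change cannot be formed.
- Unit: the research team observes lessons. No score for an individual student is described.
- Analysis: descriptive, for fidelity. No comparison of intervention and control classes on the TARE is stated. The pre-post ANOVA is limited to the two questionnaires, the PSRQ and the PACES-PE.

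**3. Look for another route to a leadership score.**
- The repeated measures multivariate ANOVA does not list its variables. It can only use scores that exist, and none is defined for leadership.
- Quantitative Analysis names TPSR beside the two questionnaires as a source of data, probably meaning the TARE. This adds no leadership score.
- The four teacher journal questions (Fidelity section) cover engagement with the responsibility themes, progress in any theme, the most successful part of the lesson, and changes. None asks about leadership by name.
- Student focus groups could yield leadership material, but as thematic text and not as a score.

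**4. Check the sample-size figure.** The Participants section gives 77 per group for 80% power at two-sided 5%, with no effect size or standard deviation, so 77 cannot be reproduced from the article's inputs. Inverted by the normal approximation, it implies a standardised difference of (1.960 + 0.842) × √(2/77) = 2.802 × 0.1612 ≈ 0.45. That value is an inference. The statement does not name the outcome it is for, so it does not show how leadership was to be measured.

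**The case against.** The strongest reply is that the account of the TARE is visibly incomplete. Measurement Tools goes straight to a second part without describing a first, and the abstract does name the TARE for the primary outcomes. A lesson-level leadership rating may exist in the part not described. This stands: a reader might infer that the TARE contains no leadership measure, and the article does not establish that. It does not rescue the plan, because the stated timing and analysis would still give no pre-post or between-group leadership effect.

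A second reply is that an article may leave scoring detail to a fuller document. That would hold if the article were silent. It is not silent: it assigns leadership to the PSRQ and then describes a PSRQ without it.

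A third reply is that the sentence in Intervention Design concerns the focus of the intervention and is not an outcome list. This is fair. It agrees with the two-construct reading but carries little weight alone.

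Two stronger readings are tempting and should not be made:
- A reader might infer an inflated false-positive rate from three primary tests at 5% each. The article states no such rule: the 5% level appears only in the sample-size sentence, and a multiplicity rule may sit in an analysis plan that is not shown. Nor can three tests be run while leadership has no score.
- A reader might infer that leadership will be assembled from items picked after the data are seen. Nothing in the article says so.

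**Conclusion.** The point holds as an internal contradiction. Leadership cannot be analysed as a primary outcome **as this protocol is written**, which is narrower than saying it could never be analysed. The defect affects one of three stated primary outcomes; the two responsibility outcomes each have a named score and a planned pre-post analysis and are untouched by it.

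The conclusion rests on the article's own description of the PSRQ as a two-category instrument, and on its schedule and analysis of the TARE. It depends on no outside knowledge of either instrument and on no assumed effect size. It should be corrected before the analysis, scheduled for October 2025, because it determines what the trial may report as a primary result.

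**What to change.** Reconcile the abstract, Outcomes, Measurement Tools and Quantitative Analysis before the data are analysed:
- State the PSRQ personal responsibility and social responsibility scores as the primary outcomes, in the same words throughout.
- Reclassify leadership as exploratory, for example from the focus groups. The teacher journals are a weak source unless a leadership question is added.
- Remove the TARE from the primary-outcome tools and keep it as a fidelity measure only.

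If leadership is to stay primary, name a measure that has already been collected, its score, and the comparison to be made. This resolves the contradiction equally well, provided such a measure exists.

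The Results section says that data collection began in August 2025, so either route is more than an edit. Date it, justify it as an outcome change, and check the registry entry against it; that record was not available here, so whether it needs amending is unknown.

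The work is modest: wording, a dated justification and the registry check. The main cost of reclassifying is that the trial can make no confirmatory claim about leadership.
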